### Intervention

Individuals in the intervention group will receive seven individual GSD-Y visits (of 1–1.5 h) with a facilitator (either a diabetes nurse or a physician) over 3 to 6 months. The facilitator is educated in the GSD-Y method. The GSD-Y method includes that the participant works with structured reflection sheets. By filling in reflection sheets before each visit and using their own words and drawings, participants systematically explore and express their own experiences and difficulties with diabetes in daily life. In addition, if the participant is under 18 years of age, her parents will be offered one individual visit and one visit together with the participant according to the GSD-Y method. The topics for the different visits are presented in Table 1. The first reflection sheet will be sent or given to the participants before the first visit. For subsequent visits, the reflection sheet for the next meeting will be distributed at that visit and completed before the next visit. In the dialogue between the participant and the facilitator, the facilitator uses different communication methods including mirroring, active listening, and value-clarifying responses. Those participants who have taken part in the first five GSD-Y visits will be considered to have completed the education. Visits are booked in consultation with each participant and, if a participant misses out of a visit, she will be offered another appointment provided she wants to continue with the study.

**Table 1 Tab1:** Overview of reflections sheets

Visit 1	Your life with diabetes from the beginning to now
	Written invitation to work together in a new way
	Two ways of looking at glycosylated haemoglobin (HbA1c)
	Agreement on things to work on
Visit 2	Your life with diabetes from the beginning to now
	Important events and periods in your life
	What do you find difficult at present living with your diabetes?
	Your plans for changing your way of life
Visit 3	Values and opportunities
	Unfinished sentences: needs, values, experiences, and opportunities
	Individual visits for parents are offered
Visit 4	Diabetes in your life
	A picture or expression describing your life with diabetes
	Room for diabetes in your life
	Shared responsibility between adolescent and parent for diabetes in daily life
	Common name for difficulty in your life with diabetes
	Agreement on things to work on until next visit
Visit 5	Problem identification and problem solving
	Current problem solving
	Dynamic problem solving
	Agreement on things to work on until next visit
Visit 6	Different ways of looking at numbers
	Blood glucose (BG) tests and your reasons for checking
	Actual BG numbers and wishes
	Your plan for BG regulation in the short and long run
	Common name for a difficulty in your life with diabetes
	Agreement on things to work on until next visit
Visit 7	Problem identification and problem solving
	Current problem solving
	Dynamic problem solving
	Solved problems and subjects to continue working on
	Visit along with parents is offered

The control group will receive standard care, which includes visits to the diabetes nurse or the physician at the unit every second to third month with closer visits if needed, according to the patient’s glycaemic control.

Participants may report any adverse events or other unintended effects of the intervention to the facilitators or to their usual HCP. If needed, further psychological support is available in the diabetes team.

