## Background

### Diabetes and female adolescents

It is well established that poor glycaemic control during adolescence and young adulthood increase the risks of acute and long-term diabetes-related complications [1]. Recommended treatment for children and adolescents with type I diabetes mellitus (T1DM) is multiple daily injections (MDI) or continuous subcutaneous insulin infusion (CSII) [2]. Intensive diabetes management has been in the clinical routine in Sweden for many years. The Swedish recommended level of glycaemic control, measured as glycosylated haemoglobin (HbA1c), for children and adolescents (<18 years) has recently changed (in 2017) from 57 mmol/mol or below to 48 mmol/mol or below without increasing the number of hypoglycaemic episodes [2]. For adults, the corresponding target is HbA1c < 52 mmol/mol [3]. To reach the recommended level it is necessary to measure blood glucose frequently or to use continuous or flash glucose monitoring (CGM/FGM). In Sweden, only around 55% of the paediatric population with T1DM reached the former HbA1c target of < 58 mmol/mol [4]. After starting school, at 7 years of age, HbA1c tends to increase with age and female adolescents have the most unsatisfactory glycaemic control of all age groups [4]. A similar pattern has also been found in other European countries [5]. Girls with T1DM report a higher disease burden, poorer perceived health, and lower quality of life (QoL) than boys [6–8], and females with T1DM face a 40% excess risk of all-cause mortality compared with men with T1DM [9]. Furthermore, women with T1DM have a significantly higher healthcare expenditure than men [10]. A nationwide study from Sweden demonstrated that female sex and high HbA1c adjacent to the diagnosis of T1DM are risk factors for poor control in young adults with increased prevalence of nephropathy and retinopathy [11]. This is in line with findings from previous studies reporting that female gender is a risk factor for microvascular complications [12–14]. Girls with T1DM have significantly higher mean body mass index (BMI) at follow-up compared with their male counterparts [15], and an elevated BMI is associated with higher levels of HbA1c [15]. Furthermore, high pre-pregnancy BMI is an important risk factor for adverse outcome in type 1 diabetic pregnancies [16]. In the report from the Public Health Agency of Sweden 2016, female adolescents (16–29 years) reported a higher degree of both mild and severe anxiety compared with their male counterparts [17]. In females with T1DM, but not in males, means of communication and a perception of being able to control the disease have been shown to be important contributing factors for achieved level of glycaemic control [18]. Furthermore, the coping strategy “ventilating negative feelings” was associated with poor metabolic control among females [18]. Active coping, in this case referring to how to rationally manage a problem, was found to be related to improved metabolic control in adolescents with T1DM [19]. On the other hand, emotion focused coping, such as behavioural disengagement and aggressive coping, was related to poor metabolic control [19]. This emphasizes the importance of finding out the patient’s coping strategies, views, and perceptions of her diabetes.

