#### Secondary outcomes

Data on self-management will be assessed by downloading data from self-monitoring of blood glucose (SMBG, CGM, and FGM). This way of measuring self-management has been shown to be effective in an earlier study [41]. Before randomization, each participant will fill in a questionnaire on socioeconomic data (occupation and family structure) and whether the patient has a neuropsychiatric disorder or other disease. The number of planned and completed visits will be collected from all participants by the patient record. All questionnaires that are used in this study are validated and have been used by our research group in previous studies.

Swe-DES 23 [36] will be used to measure the psychosocial self-efficacy of individuals with diabetes and has been validated in Sweden. Perceived self-efficacy is related to the willingness and the ability of people to engage in different behavioural challenges including managing a disease [42]. Swe-DES 23 measures willingness to change, self-awareness, problem identification, and stress management in a 23-item questionnaire and is sensitive to change.

We will use the DTSQ Teen and Parent [37] to measure treatment satisfaction. This instrument has recently been translated by our research group and validated to Swedish and is a widely used instrument internationally for measuring treatment satisfaction. “DTSQ Teen and Parent” measures treatment satisfaction on a 0 to 6 scale and enables comparison between the teenagers’ reports and their parents’ reports. “DTSQ Teen” is a 12-item questionnaire and “DTSQ Parent” is a 14-item questionnaire.

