### Data monitoring

A Data Monitoring Committee (DMC) is not used in this study. Since the study is not considered large or complex and not associated with high risk or resulting in any danger for the participants, it should not be necessary to use a DMC. There are no plans for interim analysis. The principal investigator, [name], is responsible for ny potential decision to terminate the trial.

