The intervention will take 3 to 6 months and will be performed within the ongoing care for patients with T1DM at Sachs’ Children and Youth Hospital and at Ersta Hospital in Stockholm. Sachs’ Children and Youth Hospital is the only paediatric diabetes clinic in Sweden that cares for adolescents with T1DM up to 20 years of age. The adult diabetes outpatient clinic at Ersta Hospital has the lowest average age of T1DM patients in Sweden. Thus, these centres can provide us with enough patients for inclusion in this study. It is important to note that patients with type 1 diabetes are selected to the outpatient clinics mainly by their residency area.

It cannot be ruled out that any potential effect on HbA1c levels in this study is only a consequence of increased numbers of visits to the diabetes clinic. For patients with HbA1c above 63 mmol/mol the recommendation is more frequent visits with a diabetes nurse or a physician every 4 to 6 weeks. Accordingly, many patients in the control group will also see their caregivers more often without getting the education with GSD. To investigate the effect of the number of visits, we will register both planned and completed visits for all participants.

When seeing a patient more frequently it is sometimes difficult to get the patient’s interest and to continue forward in the process of working with problem areas. It is also common that there may be late cancellations. The GSD-Y method might increase the patient’s motivation to come to the hospital and may, together, work as a tool for both patients and HCPs in supporting diabetes self-management.

Finally, the GSD method might be seen as a time-consuming method and, if it proves successful, we plan to develop a compressed version of the method in collaboration with Assistant [name] who created the GSD-Y method.

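### Adverse events rest on voluntary reports that are not comparable between arms, and no hypoglycaemia or ketoacidosis outcome is listed beside HbA1c

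*Protocol article*

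**What the plan says.** The harms rule in the Protocol article is one sentence under Intervention: "Participants may report any adverse events or other unintended effects of the intervention to the facilitators or to their usual HCP". Reporting is optional, the wording centres on effects of the intervention, and there are two recipients: the GSD-Y facilitator or the usual healthcare provider.

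Contact differs by arm. Under Intervention, "Individuals in the intervention group will receive seven individual GSD-Y visits (of 1–1.5 h) with a facilitator", over 3 to 6 months. Controls have "visits to the diabetes nurse or the physician at the unit every second to third month with closer visits if needed". The Discussion adds: "For patients with HbA1c above 63 mmol/mol the recommendation is more frequent visits with a diabetes nurse or a physician every 4 to 6 weeks", so that "many patients in the control group will also see their caregivers more often without getting the education with GSD". The Randomization section states that allocation is not blinded after randomization.

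The data list (Measures and data collection) and the outcome sections name HbA1c, body size, insulin dose, self-management and questionnaire scores. Neither hypoglycaemia nor ketoacidosis appears. Glucose downloads are taken for one stated purpose: "Data on self-management will be assessed by downloading data from self-monitoring of blood glucose (SMBG, CGM, and FGM"). The Background reports that the Swedish target for those under 18 is now "48 mmol/mol or below without increasing the number of hypoglycaemic episodes". Data monitoring explains the absence of a monitoring committee partly by the study being "not associated with high risk or resulting in any danger for the participants".

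**The concern.** A passive rule yields comparable counts only if both arms have similar opportunity and prompting to report. Here one arm has a facilitator, long structured sessions and knowledge of its allocation, and the rule is phrased in terms of an intervention that controls do not receive. Equal true harm could therefore produce unequal counts, most likely more reports with GSD-Y. A real excess could then be put down to closer contact, and a null result would mean little.

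The trial aims to lower HbA1c. If it succeeds, a reader will ask whether more low-glucose episodes came with the reduction, because the target cited in the Background carries that condition. As described, the trial is not set up to answer this. An analysis plan written later cannot fully repair it, because it cannot analyse events that were never collected.

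**Working it through.** The article gives no harms figure to reproduce. Its one computed figure, the sample size, does reproduce: 2 × (1.960 + 0.842)² × 10² / 6² = 43.6, so 44 per group, and 88 / 0.88 = 100.

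**1. Contacts over a common 6 months** (the longest stated intervention window; intervals from Intervention and Discussion)

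- Intervention: 7 visits, or 7 × 1 to 7 × 1.5 = 7 to 10.5 hours.
- Controls, standard schedule: 6/3 = 2 to 6/2 = 3 visits.
- Controls above 63 mmol/mol: 6 months is about 182.6 days; 182.6/42 = 4.3 to 182.6/28 = 6.5 visits.

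| Control schedule | Ratio if GSD-Y visits replace routine visits | Ratio if they are added |
|---|---|---|
| Every 2–3 months | 7/3 = 2.3 to 7/2 = 3.5 | 10/3 = 3.3 to 9/2 = 4.5 |
| Every 4–6 weeks | 7/6.5 = 1.1 to 7/4.3 = 1.6 | 13.5/6.5 = 2.1 to 11.3/4.3 = 2.6 |

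The article does not settle which column applies. The Discussion places the intervention within ongoing care, so the first column is the cautious one.

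**2. Contacts over 12 months.** Assume that GSD-Y replaces routine visits for 6 months and that both arms then follow the same schedule. Standard schedule: 9/4 = 2.3 or 10/6 = 1.7. Above 63 mmol/mol: 11.3/8.7 = 1.3 or 13.5/13.0 = 1.0. The imbalance is diluted but remains on the standard schedule.

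**3. What unequal contact does to volunteered counts.** Assume equal true harm in both arms and a chance p, the same at every contact, that a given harm is volunteered. The chance that it is ever reported over k contacts is 1 − (1 − p)^k. With p = 0.10:

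- intervention, k = 7: 1 − 0.9^7 = 0.522;
- controls, k = 2 and 3: 0.190 and 0.271, giving apparent ratios of 2.75 and 1.93;
- controls, k = 4.3 and 6.5: 0.364 and 0.496, giving 1.43 and 1.05.

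For p from 0.05 to 0.20 the apparent ratio runs from 3.1 to 1.6 against standard-schedule controls, and from 1.5 to 1.0 against controls seen every 4–6 weeks. The value of p is an assumption; the article gives nothing from which to estimate it.

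**4. Content of the contacts.** Table 1 has a sheet on present difficulties with diabetes at visit 2, and sheets on the reasons for glucose checks and on actual glucose values at visit 6. Controls do not receive these prompts, so equal visit counts would still not mean equal prompting.

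**5. What else could detect hypoglycaemia.** SMBG, CGM and FGM data are downloaded in both arms and registered by nurses outside the study (Measures and data collection; Secondary outcomes). These could show low readings. They do not identify episodes needing another person's help, or ketoacidosis. SMBG readings also depend on how often a participant tests, which the intervention may change.

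**The case against.** The strongest reply has five parts.

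- **The downloads exist in both arms.** This stands. A reader might infer that harms are seen only when volunteered, or that the trial cannot show anything about hypoglycaemia. The article does not support that: the downloads do not depend on volunteering and could give partial evidence. Worsening in diabetes burden, emotional health or family conflict is also measured by questionnaire in both arms. What remains is that no low-glucose measure is named, and that severe episodes and ketoacidosis lie outside the downloads.
- **Controls can report to their usual provider, and many will be seen often.** This also stands. It would be wrong to say that every control has far fewer contacts, or that GSD-Y visits are known to come on top of ordinary care. Visit counts are recorded for everyone, which helps to describe the imbalance but does not recover unreported events.
- **The hypoglycaemia condition belongs to a national target for those under 18.** Correct. It is not the trial's own definition of good control, and the adult target in the same paragraph is given without it. It still shows that the question is relevant to part of the sample.
- **No between-arm comparison of adverse events is planned.** True of the statistical section. The weakness lies in the collected data, and any harms table by arm would inherit it.
- **An article condenses a fuller protocol.** Fair as to definitions and forms. The point therefore rests on the rule that the article does state, and on its itemised data and outcome lists, not on missing detail.

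**Conclusion.** The point holds as a weakness in how harms are ascertained. On the stated schedules, and without assuming that GSD-Y visits are additional, scheduled contacts over 6 months differ 2.3- to 3.5-fold from standard-schedule controls and 1.1- to 1.6-fold from controls above 63 mmol/mol. The article does not say what share of controls falls in each group. Prompting differs as well. Volunteered events should therefore not be compared between arms. The likely direction is more reports with GSD-Y; the size cannot be computed, because no event rates or reporting probabilities are given.

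The primary HbA1c analysis and the sample size are unaffected. What is weakened is the step from a lower HbA1c to better control without added hypoglycaemia, which the listed outcomes do not address directly.

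**What to change.** 1. For every participant, extract severe hypoglycaemia and ketoacidosis from the patient record, with the same definitions, source and period (baseline to 12 months) in both arms. The record is already used for visit counts, and extraction can cover participants already enrolled. Episodes managed at home may reach the record only if mentioned at a visit, so one identical recall question at baseline and with the 6- and 12-month questionnaires would be a useful addition.
2. Prespecify one low-glucose measure from the SMBG/CGM/FGM downloads already taken. Show it by device type with the number of readings, and note that SMBG counts depend on testing frequency.
3. Report items 1 and 2 by arm as safety outcomes beside HbA1c, with confidence intervals.
4. Keep voluntary reporting, but tabulate those events separately, with the number of completed visits, and draw no between-arm inference from them.

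Cost: a few extraction fields and one table, with no new visit or procedure. The limit is precision. With 44 evaluable per arm, power for assumed event proportions of 5% versus 10% is about 14%, and for 10% versus 30% about 66%. The results are descriptive and could not establish that harm is absent.

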### Measures and data collection

Data will be collected shortly before randomization and at 6 and 12 months. At 6 and 12 months the questionnaires will be sent by mail to participants to fill in and to send back to JH in pre-addressed envelopes. If they fail to respond, the participants will be contacted by telephone. Baseline data will be used to describe characteristics of participants who discontinue.

The primary outcome is HbA1c at 12 months after the randomization. Secondary outcomes are self-management and psychosocial parameters based on questionnaires.

Data to be collected from participants includes: 1) HbA1c (DCA 2000), height, weight, and insulin dose per kilo body weight; 2) self-management (daily self-monitoring of blood glucose, downloaded data on self-monitoring of blood glucose (SMBG)/CGM/FGM); 3) data on socioeconomic background; 4) other diseases/disorders; and 5) number of planned and completed visits; 6) psychosocial self-efficacy (Swedish Diabetes Empowerment Scale (Swe-DES 23) [36]).

Data to be collected from participants and, if participant < 18 years, from parents includes: 1) treatment satisfaction (Diabetes Treatment Satisfaction Scale (DTSQ) Teen and Parent [37]); 2) perceived health and QoL (Check your health [7, 38], Disabkids [39]); and 3) diabetes-related family conflicts (Diabetes Family Conflict Scale (DFCS) [40]).

In this study masked assessors are not used. The primary outcome is a solid biochemical measure and the secondary outcomes include measurements on ordinal scales from validated questionnaires, and they should not be sensible to external influence. The other secondary outcomes (height, weight, insulin dose, SMBG/FGM/CGM) are registered by nurses not involved in the study.

#### Primary outcome

The primary outcome is HbA1c at 12 months after the randomization. HbA1c will be measured in connection with clinical visits right before randomization and at 6 and 12 months after. We define the baseline HbA1c as the mean HbA1c at randomization and 6 months prior to randomization in order to capture a representative value.

HbA1c levels will be assessed from capillary blood tests and analysed in the DCA Vantage apparatus (Siemens Healthcare Diagnostics, Upplands Väsby, Sweden).

#### Secondary outcomes

Data on self-management will be assessed by downloading data from self-monitoring of blood glucose (SMBG, CGM, and FGM). This way of measuring self-management has been shown to be effective in an earlier study [41]. Before randomization, each participant will fill in a questionnaire on socioeconomic data (occupation and family structure) and whether the patient has a neuropsychiatric disorder or other disease. The number of planned and completed visits will be collected from all participants by the patient record. All questionnaires that are used in this study are validated and have been used by our research group in previous studies.

Swe-DES 23 [36] will be used to measure the psychosocial self-efficacy of individuals with diabetes and has been validated in Sweden. Perceived self-efficacy is related to the willingness and the ability of people to engage in different behavioural challenges including managing a disease [42]. Swe-DES 23 measures willingness to change, self-awareness, problem identification, and stress management in a 23-item questionnaire and is sensitive to change.

We will use the DTSQ Teen and Parent [37] to measure treatment satisfaction. This instrument has recently been translated by our research group and validated to Swedish and is a widely used instrument internationally for measuring treatment satisfaction. “DTSQ Teen and Parent” measures treatment satisfaction on a 0 to 6 scale and enables comparison between the teenagers’ reports and their parents’ reports. “DTSQ Teen” is a 12-item questionnaire and “DTSQ Parent” is a 14-item questionnaire.

“Check your health” [7, 38] will be used to measure health distress and the burden of diabetes, perceived physical and emotional health, social well-being, and general QoL. It measures, on four vertical thermometer scales (0–100), perceived physical and emotional health, social well-being, and general quality of life as of now and, hypothetically, if the individual did not have diabetes. It is constructed to measure the burden of diabetes. The questionnaire can be completed in a short time and is easy to understand. We find it especially important to detect any change in the burden of diabetes since one expectation using the GSD method is to better identify and work with individual difficulties and contributing factors to glycaemic control, to increase acceptance of disease, and to decrease the burden of diabetes. To measure the generic health of children with chronic conditions, we will use the 37-item questionnaire “Disabkids” [39] that also has a specific 10-item diabetes module.

The Diabetes Family Conflict Scale (DFCS) [40] will be used to assess the level of diabetes-specific conflicts in families with children and adolescents with T1DM. The DFCS is a self-report questionnaire, and measures how frequently parents and adolescents argue about 19 tasks of diabetes management. Scores range from 19 to 57 where higher scores reflect more conflict. The importance of evaluating the degree of diabetes-related conflicts within families is emphasized since higher HbA1c has been shown to be more common in children from families with more conflicts [27].

